## Abstract

**Background:**

Influenza and pneumococcal vaccination can prevent disease and potentially life-threatening complications like sepsis. Elderly people have an increased risk of severe disease and therefore constitute a major target group for vaccination. To increase vaccination coverage, targeted interventions are needed that take theory-based specific determinants of vaccination behaviour into account. Moreover, message and campaign design should consider specific age-related characteristics (e.g., information processing, media use). The aim of this study is (i) to identify the specific informational and interventional needs of this risk group, (ii) to design and implement a targeted intervention aiming to decrease vaccine hesitancy, increase vaccine uptake and decrease the health and economic burden due to the respective diseases, and (iii) to measure the effect of this evidence-informed intervention on various levels.

**Methods:**

Prospective, multi-methods intervention study targeting individuals aged ≥60 years in a model region in Germany (federal state of Thuringia, 500,000 inhabitants ≥60 years old). The development of the intervention follows theory-based and evidence-informed principles: Data from a cross-sectional representative study provide insights into specific determinants of the target group’s vaccination behaviour. Additionally, media use is analysed to identify adequate communication channels for specific subgroups.

In pilot studies, the intervention materials are adapted to the specific cognitive requirements of the target group. For development and implementation of the intervention, an interdisciplinary and trans-sectoral approach is used, including psychology, communication science, design, medical science, epidemiology and various public health players. The intervention will be implemented in autumn and winter 2017/18 and 2018/19 and adjusted in between. Evaluation of the intervention includes: awareness, use and recall of intervention materials, effects on changes in determinants of vaccination behaviour, self-reported vaccine uptake, and vaccination coverage in the intervention area (primary outcomes), as well as disease incidences (secondary outcomes) and the economic burden of influenza, pneumonia, invasive pneumococcal disease and sepsis for the healthcare system (tertiary outcomes).

**Discussion:**

The data will add to the body of evidence on the effectiveness of evidence-informed vaccination campaign development as well as on the clinical and economic effects of pneumococcal and influenza vaccination. The effect of the intervention will teach valuable lessons about the principles of campaign development and evaluation, and can motivate a subsequent nationwide intervention.

**Trial registration:**

DRKS00012653. Registered 24.11.2017. Retrospectively registered.

### Influenza and pneumococcal vaccine hesitancy

In recent years, several studies and working group efforts have analysed potential determinants of vaccine hesitancy [23]. Vaccine hesitancy is defined as “(…) a delay in acceptance or refusal of vaccination despite availability of vaccination services. Vaccine hesitancy is complex and context specific, varying across time, place and vaccines” [24] (p. 4161). Reasons for vaccine hesitancy are a lack of *confidence* (distrust in vaccinations and the providing health system), *complacency* (underestimated risk of diseases or risk denialism) and/or in*convenience* (lacking or inconvenient access to vaccination) [24]. The model was further extended by *calculation* (engagement in an extensive information search for pros and cons of vaccination) [25]. This factor explains the fence-sitting effect: Individuals with high calculation show extensive information search, ending up in a situation of insecurity and confusion about risks and benefits, so that they are unable to decide and postpone their vaccination decision into the future. Finally, people may rely on herd immunity (factor *collective responsibility*). In reference to theoretical frameworks, these reasons are syndromes of psychological determinants of the vaccination decision [26].

A recent systematic review on influenza vaccine hesitancy identified lack of confidence and complacency as the most frequently reported barriers of influenza vaccine uptake in the elderly [27]. One reason for complacency, for example, might be a lack of awareness about sepsis as a severe complication of an infection. Studies indeed show that sepsis, which is the most severe and often-lethal complication of infections, remains largely unknown in the public [28]. Given this situation, awareness campaigns that address risk perceptions might be able to effectively decrease influenza vaccine hesitancy.

In contrast to influenza vaccine hesitancy, there is only minimal research addressing pneumococcal vaccine hesitancy [16] and a review of interventions is lacking [29]. Thorough knowledge about the determinants of vaccine hesitancy as well as the target group, however, is necessary for evidence-informed and targeted campaign development [26, 30, 31].

### The elderly as a target group

The elderly differ from the general public with regard to their information processing [32, 33], risk perception [34], decision quality [35] and media use [36, 37]. For example, elderly individuals process gains and losses more extremely than younger individuals [38], they favour and remember positive over negative stimuli [39], they have difficulties understanding available options in decision-making [40] and show greater risk avoidance [41]. Moreover, regarding media use elderly individuals differ from their younger counterparts. Even though the use of digital media increased constantly in people aged ≥60 years since 2012 [42], they use more traditional media for health information (e.g., [43, 44]). Even though a number of intervention studies on influenza vaccine hesitancy have been conducted for the described risk group of elderly individuals (reviews: [23, 29]), none of the interventions explicitly took specific characteristics of cognitive ageing into account. Therefore, this intervention will pay special attention to adapting the materials to the age group.

### Transdisciplinary, evidence-informed campaign design and evaluation

Health campaigns aim to change determinants of behaviour (such as knowledge, risk perceptions, attitudes) and behaviour itself. Strategy-driven planning, implementation and evaluation increase a campaign’s success [30, 31, 45–47]. Communication science, social marketing and design experts have frequently highlighted the importance of a precise analysis of the target group and campaign setting [46, 48–50]. In this context, theories and evidence from various disciplines are relevant, which is why the present intervention takes a transdisciplinary and multi-method approach. Epidemiological and medical findings provide the necessary evidence to decide which behaviours are suitable to promote health and prevent diseases (e.g. vaccination as an effective measure to prevent influenza infection). Theories and evidence on health behaviour (social and health psychology) are crucial in order to identify suitable intervention messages and strategies based on determinants of vaccination behaviour, e.g., risk perception. Evidence on information processing and cognitive ageing (cognitive and developmental psychology, design) allows adjustment of materials to the cognitive preconditions of the target group. Evidence regarding the effects of message types (social psychology, communication science, design) is needed to identify suitable message contents and strategies. Evidence on media use, leisure activities and values (communication, psychology, design) help to segment the target group [30, 51]. Finally, in order to evaluate the intervention, the aforementioned disciplines come into play again in order to assess primary cognitive and behavioural outcomes (psychology, communication science), mediating effects of media use on vaccination coverage (design) and secondary outcomes such as reduction of disease incidence (epidemiology, medicine). Moreover, to assess the reduction of the economic burden as tertiary outcome, evidence and methods from health economics are used. Thus, this study takes a transdisciplinary multi-method approach using qualitative and quantitative methods, experimental and non-experimental designs, as well as various sources of primary and secondary data (e.g., surveys, health insurance claims data). The evidence both from the literature and the evidence created in this study will be harnessed to design, improve and evaluate an intervention aiming to decrease vaccine hesitancy, increase vaccine uptake and decrease the health and economic burden due to the respective diseases.

### Status of the study at the time of submission

The status of the study is ongoing. The intervention has two waves; the first wave is completed and evaluation is currently underway. Evaluation has been completed regarding knowledge and attitudes; based on this, the intervention is currently adapted for wave 2. Evaluations based on data sources other than survey data are still pending. Wave 2 will be implemented in Fall 2018; evaluation of wave 2 will start in Winter 2018.

## Methods

### Study design and target population

In this intervention study, the population of the federal state of Thuringia, Germany, aged 60 years and above, forms the intervention group (*N* = 500,000). The intervention will take place in two consecutive influenza seasons (2017/18 and 2018/19, Fig. 1) and will be adapted in between. Changes in the outcomes will be compared to other German federal states and/or in a pre-post design depending on the outcome (specified below). Where possible, the analyses will follow a two-step analysis, first with an overall evaluation of the age group over 60 in general and then followed by analyses with special focus on the age group that will be identified as the main target group of the intervention.

**Fig. 1 Fig1:**
[figure not shown]
Overview of the Vaccination60+ study

### Development of the intervention: Inputs

The developmental process harnesses several sources of data – besides thorough literature research a cross-sectional representative survey identified determinants of vaccination and profiled the target group for the strategic planning process. The intervention is developed using a User-Centred Design Approach (user-centred design ISO 13407, [52, 53]), supporting the criteria of usefulness, usability and effectiveness. User-centred design involves focusing on the user’s needs, persona development, a general task requirement analysis, carrying out and evaluating early stage testing with the user group and follows an iterative design-process.

### Cross-sectional representative telephone survey

The data represent the base upon which the intervention is developed and, at the same time, it represents the benchmark against which the intervention’s success will be evaluated.

### Study population

*n* = 700, cross-sectional sample, representative for age over 60, rural/urban living areas, education. The sample size is selected to obtain a similar sample sizes for pre- and post-measurement. Because the post-measurement includes a two-group comparison that requires a specific sample size for statistical power justification of n for both surveys is based on the post-measurement (see below: *study population* in *evaluation of the intervention*). Dialling will be randomized for Thuringia and data are collected anonymously.

### Outcome measures

The full original questionnaire that shows the operationalisation of all measures is available via the Open Science Framework (in German; [54]). The following constructs were assessed:

### Vaccine hesitancy

Syndromes of determinants for vaccination decision-making (calculation, complacency, convenience, a lack of collective responsibility and low confidence) were assessed with a questionnaire tool based on previous work [26]. A long version was used for influenza, for pneumococcal vaccine a short version was created due to time constraints.

### Further determinants of vaccination behaviour

These measures include multi-item batteries to assess (i) knowledge about vaccines and vaccination [55] as well as sepsis, (ii) attitude towards vaccination [56], (iii) perceived risk of disease and vaccination [57], (iv) past experience with influenza and previous vaccinations, (v) received recommendation by practitioners or healthcare workers. Furthermore, we assessed modifying factors such as contextual determinants (physicians’ reachability, travel time to the physician, frequency of interaction with health service), physical determinants (self-perceived health status, chronic disease) and sociodemographic determinants (age, gender, education, employment status, marital status, income, insurance status, town size and household situation).

### Self-reported vaccine uptake and intention to vaccinate

Previous vaccination behaviour (influenza, pneumococcal) was assessed.

### Additional measures to support campaign design

Item-batteries assessed media use (conventional and new media, apps), health information search behaviour [58] and opinion leadership regarding health issues [59, 60], leisure activities and interests as well as general values [61].

### Statistical analyses

Multiple regressions to identify significant predictors of self-reported vaccination behaviour, cluster analyses to segment the target group, descriptive statistics to identify relevant media channels. In telephone surveys item non-response is common. We plan to analyse full cases only, i.e., we use listwise deletion to deal with non-response. However, we are aware that excluding missing values via listwise deletion can (a) reduce the statistical power of results and (b) induce bias if participants are not missing completely at random (MCAR). Therefore, we will only use listwise deletion if (a) the statistical power of our analysis is not substantially reduced and if (b) we find no signs for a violation of the MCAR condition. If one of the conditions is violated multiple imputation will be used to deal with missing values and imputed and non-imputed results will be reported for a transparent comparison.

### Vaccination uptake

Baseline of vaccination uptake (pneumococcal and influenza vaccine coverage) according to age, gender and region are identified based on health insurance claims data to specify target groups according to possible long-term impact and efficacy.

### Distribution of socio-demographic characteristics

Data from the Federal Statistical Office sources are examined regarding the target group’s distribution of education, status of employment, family status, size of the household, consumer panels, lifestyle values, income and health insurance type.

### Persona development

Structured interviews are conducted with prototype individuals from the target group. Data from these qualitative interviews are triangulated with all data sources mentioned above to develop a female and male persona as a reference point for ideation and development [62].

### Touchpoint analyses

Potential touchpoints for the intervention (pharmacies, physicians, leisure activities) and potential practical barriers (distance to the physician) are assessed and decided on the basis of relation of cost, reach and possible efficiency for improved vaccination uptake in reference to the persona and budget restrictions.

### Experimental studies and specific pre-testing of materials

During the development phase, quantitative and qualitative studies repeatedly explore the effects of the content, design and materials. Individuals from the relevant age group participate in these studies to take this target group’s specific cognitive, emotional and motivational characteristics into account (e.g., to test message types in the target group, to pilot whether the target groups understand and like the developed materials such as a website or a flyer, to explore the effect of certain design elements). The specific studies will be described elsewhere.

### Implementation and dissemination: Activities

The intervention will be implemented from September to February 2017/18 and 2018/19 (Fig. 1). The intervention will be adapted based upon the evaluation results of the first wave.

#### Dissemination

##### Multipliers

Physicians, pharmacists and employers can order free printed materials for dissemination. Other multipliers can also order materials; however, these former groups are the main multiplier groups.

##### Website

A website is the richest information source of the intervention (www.thueringen-impft.de). It addresses all relevant reasons for vaccine hesitancy. All printed materials relate to the website.

##### Out of home media and advertising

Several advertisements in special interest media and in outdoor areas will be evenly distributed throughout the intervention region. Flyers and posters (distributed at train stations and on buses) as well as radio spots are used to increase the visibility of the intervention, spread the slogan and attract people to the intervention website.

##### Press coverage

Press releases, interviews and reports appear in print and online media as well as radio.

#### Tracking

In order to evaluate the impact of the different materials it will be necessary to track the distribution ways of the materials. For the printed materials, there will be an online ordering service, which allows tracking of the location where the printed materials were ordered. Online tracking of a central intervention website will deliver further information about the regional access. These sources will allow calculation of a correlation between the amount of distributed materials/frequency of website use and vaccine uptake per sub-region. The data will be stored according to current standards of European law. Additionally, media monitoring allows for tracking of media reports and their potential effect on awareness and perception to control for external influences and contributes to reliability and validity of the interventions’ evaluation.

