##### Statistical analyses

Different methodological approaches will be considered to calculate vaccine uptake before and after the intervention. First, coverage will be calculated as the proportion of patients vaccinated per year (pneumococcus vaccination) or per season (influenza vaccination). The denominator will be taken from the KM6 statistics [65]. Second, vaccine uptake will be calculated among selected patients in a cohort approach [66]. Vaccine uptake will be calculated among those individuals who were < 60 years of age at the beginning of the observation period and turn 60 thereafter (thus have a new indication for the vaccine). For pneumococcus vaccination only, vaccine uptake will also be calculated for at-risk groups who have not been vaccinated in the last 5 years before the respective calendar year of interest and are thus recommended to receive the vaccine.

Vaccine uptake for both influenza and pneumococcus will be analysed by age, district, year/season/month and chronic underlying conditions (based on ICD-10 codes).

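### The planned sub-region correlation of materials and website use with vaccine uptake names no adjustment for prior uptake, so existing differences between sub-regions can create or mask an apparent dose-response.

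*Protocol article*

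**What the plan says.** The Tracking section gives its purpose at the outset: "In order to evaluate the impact of the different materials it will be necessary to track the distribution ways of the materials". For print, "there will be an online ordering service, which allows tracking of the location where the printed materials were ordered"; for the website, regional access is recorded. These sources are to permit "calculation of a correlation between the amount of distributed materials/frequency of website use and vaccine uptake per sub-region". The one control named there is for press activity: "media monitoring allows for tracking of media reports and their potential effect on awareness and perception to control for external influences".

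The Multipliers section says how the printed dose arises: "Physicians, pharmacists and employers can order free printed materials for dissemination". It adds: "Other multipliers can also order materials; however, these former groups are the main multiplier groups". The section on out-of-home media says that the advertisements will be "evenly distributed throughout the intervention region".

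Two other places bear on the point. The Vaccination uptake section, among the inputs to the intervention's development, obtains baseline coverage by region from claims data. The statistical analyses for the coverage outcome state: "Vaccine uptake for both influenza and pneumococcus will be analysed by age, district, year/season/month and chronic underlying conditions". Neither is linked to the tracking correlation.

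**The concern.** The tracked amount of print is the result of choices made by the people who order it. Engagement with vaccination is a plausible common cause of ordering leaflets and of high local uptake. If so, sub-regions that already had high uptake would show both more material and more vaccination even if the campaign did nothing. If low-uptake areas order more, the same analysis would hide a real benefit. Website use is also self-selected, but by users and not by orderers. Advertising that is spread evenly adds little regional contrast. Media monitoring deals with press reports and not with earlier uptake.

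At stake is how this analysis is read. The other links between exposure and outcome inside Thuringia rest on recall in the surveys; this is the stated analysis that ties recorded delivery to uptake. A correlation reported under the purpose of evaluating impact could be taken as evidence of effect when it shows only where uptake was already high.

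**Working it through.** **The plan's own figure.** None. The document gives no number of sub-regions, no significance level and no expected size for this correlation. What follows is an illustration on stated assumptions.

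**Inputs from the document.** The exposure is the amount distributed or website use, per sub-region. The outcome is uptake per sub-region. Ordering is voluntary. No adjustment for earlier uptake is named.

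**Assumed inputs.**
- Number of sub-regions K: 10, 20 or 40.
- Correlation ρ between ordering and prior uptake: −0.5, 0, 0.3, 0.5 or 0.7.
- Stability s, the correlation of a sub-region's uptake before and after: 0.8 or 0.95.
- True effect of materials: zero.
- Test: two-sided at 5%.

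**Model (standardised).** Orders = ρ × prior + √(1 − ρ²) × noise. Post-campaign uptake = s × prior + √(1 − s²) × noise. The expected crude correlation is therefore about ρ × s. For example, 0.5 × 0.8 = 0.40 and 0.5 × 0.95 = 0.475.

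**Crude correlation, K = 20, 4,000 runs per setting.**

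| ρ | mean r (s = 0.8 / 0.95) | significantly positive | significantly negative |
|---|---|---|---|
| −0.5 | −0.39 / −0.47 | 0.1% / 0.0% | 43% / 60% |
| 0 | 0.00 / −0.01 | 2.8% / 2.0% | 2.3% / 2.4% |
| 0.3 | 0.23 / 0.28 | 17% / 23% | 0.2% / 0.1% |
| 0.5 | 0.39 / 0.46 | 43% / 60% | 0% / 0% |
| 0.7 | 0.55 / 0.65 | 76% / 92% | 0% / 0% |

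At ρ = 0.5 the false-positive share runs from 21% (K = 10, s = 0.8) to 89% (K = 40, s = 0.95).

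A second simulation used 20 sub-regions, a between-district SD of 5 points and a season-to-season SD of 1.5 points. It gave 23%, 60% and 93% for ρ = 0.3, 0.5 and 0.7. The two simulations together give the range of 17% to 93%.

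**After conditioning on prior uptake.** The partial correlation averages about zero. It is significant in about 4% to 6% of runs in every setting, against the nominal 5%.

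**Limit of that result.** The return to 5% follows because measured prior uptake is the only confounder in the model. Suppose instead that orders correlate 0.7 with a stable underlying uptake (SD 5), and that each season adds independent noise (SD 1.5).
- Reliability of one season = 25 / (25 + 2.25) = 0.917.
- r(orders, pre) = r(orders, post) = 0.7 × √0.917 = 0.670, and r(pre, post) = 0.917.
- Partial r = (0.670 − 0.670 × 0.917) / √[(1 − 0.670²)(1 − 0.917²)] ≈ 0.19.

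If three pre-campaign seasons are averaged, the noise variance is 2.25 / 3 = 0.75.
- Reliability = 25 / 25.75 = 0.971.
- r(orders, pre) = 0.7 × √0.971 = 0.690.
- r(pre, post) = √(0.971 × 0.917) = 0.944.
- Partial r = (0.6705 − 0.6897 × 0.9438) / √[(1 − 0.6897²)(1 − 0.9438²)] ≈ 0.08.

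Adjustment for one season reduces the bias but does not remove it; averaging several seasons reduces it further.

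**The case against.** The strongest reply is that the Tracking section describes what the data will make possible, within an account of implementation. It does not say whether the amount is raw or per head, or that adjustment is ruled out, and a condensed article may leave such details to an analysis plan that is not shown. Baseline uptake by region and uptake by district and season are already planned, so an analysis of change would be compatible with the text. This has weight, and it limits the point. It does not remove it: the section names an exposure, an outcome, a statistic, a purpose and one control, and that combination, followed as written, does not serve the purpose.

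Several stronger readings are tempting, and the document does not support them:

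- **That existing differences will look like a benefit.** This needs ordering to be positively related to prior uptake. No section says so; with no relation there is no bias from this source, and with a negative relation it is reversed.
- **That the orderers are vaccinating practices and pharmacies.** Employers are a main multiplier group, other multipliers may order, and nothing says that pharmacies vaccinate.
- **That district size inflates the correlation.** Coverage is a proportion. A dose that grows with population biases the result only if coverage also varies with district size, which is not stated and was not simulated.
- **That most of the tracked variation comes from orders.** Even distribution is stated for advertisements; website access is tracked separately.

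**Conclusion.** The point stands for a supplementary analysis. As described, the correlation cannot separate an effect of the materials from differences in uptake that were there before. On the assumptions shown, the false-positive share is about 17% to 93% when ordering correlates 0.3 to 0.7 with prior uptake. It stays at the nominal level when they are unrelated, and a negative relation would mask a benefit. The inputs are assumed throughout, so the figures show how sensitive the analysis is and do not predict its result.

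A reader might infer that the campaign's main evaluation is compromised. It is not. The coverage hypothesis rests on comparison with the pre-intervention period and with other federal states, and the adaptation for wave two relies on the representative survey. Neither uses this correlation.

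**What to change.** In the Tracking section, replace the correlation with a district-level regression:

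- **Outcome:** post-campaign uptake in the district.
- **Exposure:** materials ordered per 1,000 residents aged 60 or over, and website visits per 1,000 residents.
- **Adjustment:** the same district's pre-campaign uptake, preferably averaged over several pre-campaign seasons where these are available.
- **Reporting:** call the result an association, not a measure of impact.

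The cost is a change of wording and a little more analysis. The claims data carry district of residence, baseline uptake by region is already planned, and population counts can come from official statistics. The remaining weakness should be stated with the result: one measured prior season does not remove all stable differences between districts, so residual confounding can persist.
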